**Keep it safe**

Being active is usually quite safe. But in rare cases, problems can arise (such as with running or jogging). The best approach is to prevent problems and keep it safe. Contact your doctor with any questions.

**Prevent sore muscles or cramps.**

[figure not shown]
 Only increase how often, how hard, and how long you’re active. a little at a time

[figure not shown]
 Wear good and comfortable shoes.

[figure not shown]
 Drink plenty of water before, during, and after being active.

[figure not shown]
 Wear socks that fit well, are comfortable, and keep your feet dry.

- Warm-up before and cool-down after every activity.

| **Warm-up** (Most warm-ups take only 5 to 15 minutes.)   - Do whatever activity you plan to do but at a lower intensity (lower heart rate) for a brief time. This may mean walking slowly for a few minutes before speeding up. - Do a few minutes of mild stretching if you plan to do something more vigorous than walking.     **Cool-down** (Most cool-downs take only 5 to 15 minutes.)   - Do whatever activity you have been doing, but at a lower intensity (lower heart rate) for a brief time. - Do a few minutes of mild stretching, especially if you’ve done something more vigorous than walking. |
| --- |

**
[figure not shown]
 If you do get a muscle cramp:** Stretch the muscle, then massage it. Repeat.

**
[figure not shown]
** If there is still pain, put ice on the cramp for a few minutes.

**
[figure not shown]
** Then repeat the massage and stretching.

**Stretch those Muscles**

Your body is like a rubber band.

Your muscles will become less flexible as you age and when you are not active. This makes movement more difficult. For this reason, stretching is important.

Stretching is one of the best ways to prevent and avoid muscle soreness, cramps, and hurting yourself. Stretching also helps you be more flexible and feel relaxed.

**How to properly stretch**

[figure not shown]
 Do a short warm-up *before* stretching.

[figure not shown]
 Move slowly until you feel the muscle stretch. A safe stretch is gentle and relaxing.

[figure not shown]
 Hold the stretch steady for 15 to 30 seconds. Do NOT bounce.

[figure not shown]
 Relax. Then repeat 3 to 5 times.

[figure not shown]
 Stretch within your own limits. Don’t compete.

[figure not shown]
 Breathe slowly in and out. Do NOT hold your breath.

- Relax, enjoy, and feel good about yourself.

**Important**: Never stretch if you have pain before you begin.

If a stretch causes pain, stop doing it.

**How hard are you working?**

Most people have a good sense of how hard they are working when they’re being active. Listen to your body.

Rate yourself on the following scale while you’re being active.

|  |  |  |  |  |  |  |
| --- | --- | --- | --- | --- | --- | --- |
| Very, Very Light? | Very Light? | Fairly  Light? | Somewhat  Hard? | Hard? | Very Hard? | Very, Very Hard? |
| ***Examples:*** | | | | | | |
| “I’m not  working hard  at all. I can talk and even sing easily.” | | “I’m working and breathing a little harder than usual. I can still talk easily.” | “I’m working and breathing somewhat hard. I can talk fairly easily.” | “I’m working hard and breathing deeply. I can still talk.” | “I’m working very hard. I can’t catch my breath or talk.” | |
|  | |  | | |  | |

**Right now:**

- **Stay in the range between “fairly light” and “somewhat hard.”**

Over time, you may be able to progress to the range between “somewhat hard” and “hard.”

**When to stop exercising**

Being active is usually quite safe. But in rare cases, problems can happen.

Be aware of some of the signs and symptoms of when to stop exercising.

- **Chest pain or discomfort**

What: Uncomfortable feeling of pressure, pain, squeezing, or heaviness

Where: Possibly in the:

- Center of the chest,
- Spread throughout the front of the chest, or
- Spreading to the shoulder(s), arm(s), neck, and back

What to do: **Stop and rest.**

- If it doesn’t go away after 2-4 minutes, go to an emergency room or call 911.
- If it does go away, but returns each time you exercise, see your doctor.
- **Unusual shortness of breath, sweating, feeling lightheaded, or feeling sick to your stomach.**

What to do: **Stop and rest.**

- If it doesn’t go away after 2-4 minutes, go to an emergency room or call 911.
- If it does go away, but returns each time you exercise, see your doctor. These may or may not be signs of something serious like a heart problem.

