**Waist Circumference**

**Procedure**

Instruct the participant to gather his or her shirt above the waist, cross the arms, and place the hands on opposite shoulders. Demonstrate the desired position of the arms. It may help to tell participants to think of giving themselves a hug. If necessary, lower the pants and underclothing to slightly below the waist. Again, always tell the participant what you are going to do before you do it.

Stand on the participant’s right side. Palpate the hip area to locate the right ilium of the pelvis. With the cosmetic pencil draw a horizontal line just above the uppermost lateral border of the right ilium. Cross this mark at the midaxillary line, which extends from the armpit down the side of the torso. Exhibit 3-9 shows the measurement site correctly marked for the waist circumference.

Extend the measuring tape around the waist. Position the tape in a horizontal plane at the level of the measurement mark, and ensure the horizontal alignment of the tape. Check that the tape sits parallel to the floor and lies snug but does not compress the skin. Always position the zero end of the tape below the section containing the measurement value. Take the measurement to the nearest 0.1 cm at the end of the participants.

4. Physical Activity Assessment. Study participants will be asked to respond to a physical activity readiness questionnaire (PAR-Q) [Appendix E) for safety reasons before beginning any physical activity regime. Accelerometers and Pedometers will be provided and used to measure physical activity and to increase steps.

Acceleromter Procedure

The ActiGraph accelerometer will be used to determine physical activity at baseline and at follow-up as follows:

The measurement of physical activity pattern and volume, specifically minute-by-minute participation in different intensities of physical activity. The equipment used is the ActiGraph GT3X manufactured by ActiGraph, of Ft. Walton Beach, FL ([www.theactigraph.com](http://www.theactigraph.com/)), and previously distributed as the GT1M, the 7164, the MTI, and the CSA. An ActiGraph User Manual is also available for download from this website.

Process Overview

1. Charging accelerometer
2. Initializing accelerometer (preparing the device to collect data)
3. Instructing the participant on self-monitoring procedures
4. Downloading data
5. Preparing electronic files for archiving

Procedure

1. Charging accelerometer

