**Physical Activity Readiness Questionnaire (PAR-Q)**

For most people, physical activity should not pose any problems or hazard. PAR-Q has been designed to identify the small number of adults for whom physical activity might be inappropriate or those who should have medical advice concerning the type of activity most suitable.

| 1. | Has your doctor ever said you have heart trouble? | Yes | No |
| --- | --- | --- | --- |
| 2. | Do you frequently suffer from pains in your chest? | Yes | No |
| 3. | Do you often feel faint or have spells of severe dizziness? | Yes | No |
| 4. | Has a doctor ever said your blood pressure was too high? | Yes | No |
| 5. | Has a doctor ever told you that you have a bone or joint problem such as arthritis that has been aggravated by exercise, or might be made worse with exercise? | Yes | No |
| 6. | Is there a good physical reason not mentioned here why you should not follow an activity program even if you wanted to? | Yes | No |
| 7. | Are you over age 65 and not accustomed to vigorous exercise? | Yes | No |

**If a person answers yes to any question, vigorous exercise or exercise testing should be postponed. Medical clearance may be necessary.**

Signature Date

Witness Date

[name] Date

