**When exercising, watch for:**

- **Unusual foot pain or numbness**
- **Severe muscle soreness**
- **Joint pain or swelling**
- **Blisters, ulcers, redness or tenderness**

What to do: Call your doctor if these occur.

For now, **start slowly** and **gradually slow down** when you are finished.

[figure not shown]

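### The exercise booklet sends a participant whose exertional chest pain settles with rest to a doctor only if it recurs at every session, so a first or occasional episode carries no instruction to seek medical advice

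*Protocol*

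**What the plan says.** Appendix F, under When to stop exercising, deals with two groups of symptoms: chest pain or discomfort, and unusual breathlessness, sweating, light-headedness or nausea. In both groups the participant is told to stop and rest, and to seek emergency care if the symptom has not gone after 2-4 minutes. If it does settle, one further rule applies, printed once for each group: "If it does go away, but returns each time you exercise, see your doctor". The second group ends with a caution: "These may or may not be signs of something serious like a heart problem".

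The next part of the booklet lists foot pain or numbness, bad muscle soreness, sore or swollen joints, and blisters or similar skin problems. There the rule is "What to do: Call your doctor if these occur".

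Two other texts bear on the point. The Keep it safe part of the booklet says "Contact your doctor with any questions". The PAR-Q in Appendix E is completed "for safety reasons before beginning any physical activity regime". Its second and third items ask "Do you frequently suffer from pains in your chest" and "Do you often feel faint or have spells of severe dizziness". A positive answer has this consequence: "If a person answers yes to any question, vigorous exercise or exercise testing should be postponed. Medical clearance may be necessary".

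**The concern.** The rules for a symptom that persists are sound. The weak part is the rule for one that settles. It makes recurrence at every session the condition for seeing a doctor, and does not say how many sessions that means. A participant who follows it exactly can rest through an episode of chest pressure, resume the same activity, and learn whether the condition is met only by exercising again.

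Other study materials encourage repeated activity. The booklet asks for activity on most days, and the pedometer sheet used in the intervention arm sets a daily step target. Participants are aged 35-64 with a BMI of 25 to under 35, and the Statistical Analysis section describes the population as sedentary. What is at stake is participant safety during the study. No estimate or test depends on it.

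**Working it through.** No formula tests a safety instruction, so the check is to follow each possible course of a symptom through the booklet, then look elsewhere in the protocol for a rule that covers what is left.

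**Courses after stopping and resting (the same for both symptom groups)**

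1. Not gone after 2-4 minutes: emergency care.
2. Settles, and recurs at every session: see a doctor.
3. Settles, and is a first or only episode: no further instruction.
4. Settles, and recurs at some sessions but not others: no further instruction.

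Courses 3 and 4 are the gap. At the first episode a participant cannot tell course 2 from courses 3 and 4.

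**Texts that might fill the gap**

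- Keep it safe, in the same booklet, is a general invitation to ask a doctor questions. It names no symptom, and the specific rule that comes later sets a stricter condition.
- The musculoskeletal and skin list asks for a call on occurrence. It does not cover chest symptoms, but it shows that the booklet uses a lower threshold for complaints that are usually less serious.
- The PAR-Q is an entry screen. It does not address symptoms that first appear after entry.
- The pedometer and accelerometer instructions give a telephone number for questions, and the calendar asks each day about injury or sickness. Neither tells a participant with a resolved symptom to contact a doctor or to pause.

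None of these gives an instruction for course 3 or 4.

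**Comparison with the entry screen**

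The PAR-Q items ask about frequent chest pain and about feeling faint often. Chest pain at most sessions, but not all, would be a positive answer at entry and would postpone vigorous exercise. If the same pattern began during the study, it would not meet the booklet's every-session condition. The comparison goes no further: a single or rare episode would be answered no on the PAR-Q, so the PAR-Q gives no support for acting on a first episode.

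**Extent of exposure**

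Appendix C gives 60 volunteers, 30 per group, and three weeks of 7 days. The Intervention Phase section gives the educational materials to both groups after the first week. Exposure is therefore at most 60 × 14 = 840 participant-days. This bounds the time during which the rule applies. It does not count events.

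**The case against.** The strongest reply is that screening and intensity limits keep the risk small. The Exclusion Criteria list cardiovascular conditions, and Appendix C requires a no for heart disease, diabetes, stroke, cholesterol medication and a doctor's limit on activity. The booklet keeps effort between fairly light and somewhat hard, about a brisk walk, and participants follow it for roughly two weeks. All of this stands and lowers the risk. It does not cover symptoms that first appear during the study, which is what this part of the booklet is for.

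The contrast with blisters and sore joints can also be pressed too far. Those complaints do not usually clear after minutes of rest, so a branch for resolved symptoms would make little sense there. The booklet is also stricter about chest symptoms that persist. The contrast shows uneven thresholds, and the case does not rest on it.

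The second symptom group includes sweating, breathlessness and nausea. Whether every brief episode needs a doctor is a clinical threshold that the protocol does not supply, so the case is weaker there than for chest pain. Even so, the booklet itself says these symptoms may point to a heart problem.

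A reader might infer that participants receive no medical advice at all, or that the trial lacks safety instructions or a reporting route. The documents do not support that. The booklet says to stop and rest, gives an emergency rule and invites questions to a doctor. Pages following the Human Subjects text and the consent pages are not in the copy reviewed and may say more. A reader might also infer that the trial's results are affected, but nothing in the protocol shows that.

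**Conclusion.** The point holds for the booklet. Chest pain or discomfort that settles with rest leads to a doctor only if it recurs at every session, and a first or intermittent episode carries no instruction beyond stopping and resting. The same gap exists for the second symptom group, with less force.

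Its size is two lines of participant material given to both arms. No event rate is stated, so no number of affected participants is claimed, and no analysis or sample-size figure changes. The conclusion assumes that participants follow the booklet as written. If the pages not seen contain a stricter rule, the booklet should be brought into line with it. This is a cheap improvement to participant safety.

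**What to change.** For chest pain or discomfort, replace the recurrence line with: *Even if it goes away, do not exercise again until you have contacted your doctor. If it has come back, see your doctor.* The instruction should cover all exercise. A limit to hard exercise would still allow the same brisk walk, because Hard is a named level above the range the booklet recommends. The second sentence keeps the present advice to see a doctor when the pain recurs.

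For the second symptom group, at minimum change the every-session condition to *comes back*. Preferably, use the chest pain wording there too.

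Make the change in the booklet, which both arms receive. A separate line on the pedometer goal-setting sheet would reach only the arm that uses a pedometer during the study.

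The cost is some extra doctor contacts and possibly a few paused days, some of which may fall in the follow-up accelerometer week. For scale, assume the outcome is averaged over all 7 days for 30 participants per arm (30 × 7 = 210 participant-days) and that a paused day loses 30 to 60 minutes of moderate-to-vigorous activity. One paused day then lowers that arm's mean by 30/210 = 0.14 to 60/210 = 0.29 min/day, and five lower it by 150/210 = 0.71 to 300/210 = 1.43 min/day. The number of such days is unknown. Participants should note the reason for a pause on the calendar.

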**When exercising, watch for:**

- **Unusual foot pain or numbness**
- **Severe muscle soreness**
- **Joint pain or swelling**
- **Blisters, ulcers, redness or tenderness**

What to do: Call your doctor if these occur.

For now, **start slowly** and **gradually slow down** when you are finished.

[figure not shown]
**Next steps**

[figure not shown]
 Record only the time you are *doing* the activity (Don’t include breaks).

[figure not shown]
 Achieve your target goals.

[figure not shown]
 Walk (or do something like walking) to achieve the physical activity recommendations.

If you have a concern about too much too soon, then start slowly and work up to the recommendation at your own pace**.**

- Include a friend or family member if you like.
- Plan activities you LIKE to do.

Make a **plan for how active you will be** next week:

|  | **What I will do** | **When** | **Minutes** |
| --- | --- | --- | --- |
| Monday |  |  |  |
| Tuesday |  |  |  |
| Wednesday |  |  |  |
| Thursday |  |  |  |
| Friday |  |  |  |
| Saturday |  |  |  |
| Sunday |  |  |  |
| **Total minutes for the week (30 minutes or more):** | | |  |

EXERCISE AND FITNESS WEBSITES

[www.aahperd.org](http://www.aahperd.org/) American Alliance for Health, Physical Education, Recreation, and Dance. Provides links to American Association for Active Lifestyles and Fitness, American Association for Health Education, American Association for Leisure and Recreation, National Association for Girls and Women in Sport, National Association for Sport and Physical Education, and the National Dance Association.

[www.acsm.org](http://www.acsm.org/) American College of Sports Medicine. This is the homepage of the largest, most respected sports medicine and exercise science organization in the world.

[www.acefitness.org](http://www.acefitness.org/) American Council on Exercise. This not-for-profit organization sets certification standards for exercise professionals and runs a consumer fitness hotline offering referrals to ACE certified personal trainers. Their web site features information about their programs, referrals to fitness resources and news about exercise and fitness.

[www.cascade.org](http://www.cascade.org/) This site is loaded with bicycling websites all over the world. Nearly anything you might want to know regarding bicycling can be accessed from this page.

[www.fitnessworld.com](http://www.fitnessworld.com/) This site provides information about exercise books and videos, recent news highlights related to health and fitness, and answers to frequently asked questions about fitness.

[www.ncppa.org](http://www.ncppa.org/) National Coalition for Promoting Physical Activity. This is a premier organization in the country to promote physical activity. The objective of NCPPA is to unite the strengths of public, private and industry efforts into a collaborative partnership to inspire Americans to lead physically active lifestyles to enhance their health and quality of life.

[www.physsportsmed.com](http://www.physsportsmed.com/) The Physician and Sports Medicine Online. This website features abstracts from the current issue of the magazine, actual articles from previous issues, a search feature to find selected topics from back issues, and a Personal Health section with patient-oriented articles on exercise, nutrition and injury prevention.

[www.rrca.org](http://www.rrca.org/) Road Runners Club of America. Novice and experienced runners alike will find a vast array of information provided by this not-for-profit organization, including a calendar of events, guidelines for putting on a race, how to start a club and tips for running safely.

[www.runningpage.com](http://www.runningpage.com/) The Running Page. This site contains information about upcoming races, race results, places to run, running related products, magazines, and other information.

[www.runnersworld.com](http://www.runnersworld.com/) Runner’s World Online. This site contains a wide variety of information about running, including tips for beginning runners, advice about training, and a shoe buyer’s guide.

[www.scoi.com](http://www.scoi.com/) Southern California Orthopedic Institute. This site provides information about a variety of orthopedic problems, including those relating to back and joint injuries.

[http://fiat.gslis.utexas.edu](http://fiat.gslis.utexas.edu/) An excellent jump site to women’s sports pages around the www. Some of the topics include women’s sports, organizations, and issues in women’s sports.

[www.dstc.edu](http://www.dstc.edu/) This website is devoted to a collection of abdominal fitness FAQs on shaping your abdomen.

[http://sln.fi.edu](http://sln.fi.edu/) This site is all about how getting started with an exercise program. It also includes info on selecting a fitness center, exercise equipment, guidelines for beginners, and different kinds of exercises.

[www.fitnessonline.com](http://www.fitnessonline.com/) This site provides info on exercising and proper nutrition. It also has an online trainer as well as fitness calculators.

[www.womenfitness.net](http://www.womenfitness.net/) An online guide to healthy living and optimal fitness for women. This site also provides useful fitness tools to use in addition to articles to read.

[http://exercise.about.com](http://exercise.about.com/) This site provides extensive info on exercise and lots of resource info including a personal trainer on the Internet.

[figure not shown]

Study Forms

***USING YOUR PEDOMETER***

# Getting Started

|  | [figure not shown] |  |
| --- | --- | --- |

**Beginning tomorrow:**

Tomorrow, put your pedometer on, reset it to zero, and go about your day without changing a thing. This is very important so that you can establish your usual, or baseline, activity. Write down the number of steps you take that first day here: ___________

**Figuring out your steps:**

Now, let’s figure out how many steps you take in 10 minutes of continuous walking. So, put your pedometer on, reset it to zero, check the time on your watch, and walk at your normal pace for 10 minutes. How many steps do you take in 10 minutes? ___________________

A good rule of thumb is that 1000 steps/minute taken in 10 minutes is equivalent to walking at a moderate intensity pace. Look at your number and determine whether you need to walk a bit faster to meet the moderate intensity recommendation.

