The focus of the statistical analysis for **Non-Hypothesis 3** will be on determining the number of steps associated with reaching the DG physical activity recommendations of 60 minutes a day of moderate-to-vigorous physical activity. General linear mixed models will be used to assess the cross-sectional relationship between daily number of steps (from pedometer) and minutes of moderate-to-vigorous physical activity (from accelerometer) using data collected post-intervention on all subjects in the intervention group. A mixed model approach is required to incorporate all seven days worth of data collected on each participant. The number of steps corresponding to 60 minutes of moderate-to-vigorous physical activity will be determined, and potential gender differences in the target number of steps will be examined. If significant gender differences exist, gender-specific step targets will be calculated and used in the future effectiveness study.

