**How many steps are enough?**

A good guideline is to add 60 minutes of moderate intensity activity, like brisk walk, to your usual daily activities. This is equivalent to an additional 6000 steps. But it also depends on your baseline activity.

- If you take less than 5,000 steps/day at baseline, add 6,000 steps/day
- If you take between 5,000 and 7,500 steps/day at baseline, add 3,000 steps/day
- If you already take more than 7,500 steps/day at baseline, consider adding more steps/day and/or walking faster.

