**Setting your goal**

Add the amount of steps you plan to increase by_____________ to your baseline steps________________. This is your step goal equivalent to public health guidelines for physical activity. Now wear your pedometer and try to hit this target every day. The most important strategy is to look at your pedometer frequently throughout the day and see how you are doing. Also be sure to write down the steps you take each day on the calendar we gave you.

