# INSTRUCTIONS

**Pedometer:** The pedometer counts your steps taken. This pedometer resets automatically at midnight each night. You do not need to reset it. Don’t worry if it the screen reads zero when you put it on in the morning.

Wear your pedometer during your waking hours. Do not wear it in the shower or bath, or while swimming.

**Every morning**, when you put the pedometer on:

Write down the date of the day, and the time you put your pedometer on in the calendar we gave you.

Then clip the pedometer to your waistband on the front of your body near your hipbone. You can wear the pedometer under your clothes or on the outside of your waistband if you wish. Remember to use your safety clip!

**Every night when you get ready for bed**, take the pedometer off and open it. On your calendar, write down the time you took the pedometer off. Write down the number of steps shown on the screen on your daily activity calendar. YOU DO NOT NEED TO RESET IT.

Circle Y=”YES”, or N=”NO” in answer to each of the questions on your calendar.

For example, Were you injured or sick today?

Did you go to work today?

Did you do any sports today?

Did you exercise today?

If you did sports or exercise, write down the type of activity you did, and how much time you were active.

For example,

Walk 30 minutes

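### The participant handouts contradict themselves on walking cadence, on the minutes target and on resetting the pedometer

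*Protocol*

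**What the plan says.** All references are to the Protocol.

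**Cadence.** In Using Your Pedometer, under Figuring out your steps, the participant counts steps over a 10-minute walk and then reads: "A good rule of thumb is that 1000 steps/minute taken in 10 minutes is equivalent to walking at a moderate intensity pace". The participant is to judge from their own number whether to walk faster. The next section, How many steps are enough?, suggests adding 60 minutes of moderate activity and says of it: "This is equivalent to an additional 6000 steps".

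**Goals and minutes.** The same section sets the increment by baseline. Below 5,000 steps a day the increment is 6,000. The middle tier reads: "If you take between 5,000 and 7,500 steps/day at baseline, add 3,000 steps/day". Above 7,500 the advice is open-ended. Setting your goal then says of the resulting target: "This is your step goal equivalent to public health guidelines for physical activity".

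The education booklet (Appendix F), whose materials go to both arms according to Intervention Phase, lists several guideline amounts under What are the recommendations?. They include at least 30 minutes above usual activity on most days, and about 60 minutes on most days. The blank planner under Next steps closes with the line "Total minutes for the week (30 minutes or more". Statistical Analysis, under Non-Hypothesis 3, refers to the "DG physical activity recommendations of 60 minutes a day of moderate-to-vigorous physical activity".

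**Reset.** The handout tells participants to zero the device on the first day (Beginning tomorrow) and again for the 10-minute walk: "put your pedometer on, reset it to zero, check the time on your watch". The written pedometer instructions say the device resets itself at midnight: "You do not need to reset it". The staff procedure for the NL-1000 also says that no end-of-day reset is required.

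**The concern.** With the pedometer and the personal instruction, these handouts are what the trial delivers. If cadence, step goal and minutes target do not agree, two participants can follow the materials faithfully and aim at different amounts of activity. A participant may also meet every written goal without reaching the 60 minutes a day named in Statistical Analysis. A low achievement rate could then reflect the materials rather than the feasibility of the guideline. The planner goes to both arms. The cadence sentence, the step goals and the reset wording belong to the pedometer material.

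The reset conflict concerns data as well as instruction, because the number recorded at bedtime is the day's step count.

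**Working it through.** Only unit arithmetic is needed. No sample-size or power formula is involved.

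**1. Cadence.** Inputs: 6000 steps for 60 minutes (How many steps are enough?) and 1000 steps per minute over 10 minutes (Figuring out your steps).

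- Rate implied by the step equivalent: 6000 / 60 = 100 steps per minute, or 100 × 10 = 1000 steps in 10 minutes.
- Printed rate taken literally: 1000 × 10 = 10,000 steps in 10 minutes, and 1000 × 60 = 60,000 in 60 minutes. This does not reproduce 6000; the ratio is 60,000 / 6000 = 10.
- Printed figure read as a 10-minute total: 1000 / 10 = 100 per minute, and 100 × 60 = 6000. This reproduces the handout's figure exactly.

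**2. Weekly planner.** Inputs: 30 minutes a week (Next steps); 30 or 60 minutes on most days (What are the recommendations?); 60 minutes a day (Statistical Analysis). The documents do not define most days; 4 to 7 days is assumed.

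| Daily minutes | 4 days | 7 days | Ratio to planner's 30 |
| --- | --- | --- | --- |
| 30 | 120 | 210 | 4 to 7 |
| 60 | 240 | 420 | 8 to 14 |

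The planner's figure spread over a week is 30 / 7 ≈ 4.3 minutes a day. The 14-fold end of the range is 60 minutes on all seven days.

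**3. Step tiers.** At the handout's own 100 steps per minute, the two fixed increments are 6000 / 100 = 60 minutes and 3000 / 100 = 30 minutes. Both are additions to usual activity. Someone in the middle tier who meets the goal at that pace reaches 60 minutes in total only if the usual day already holds 60 − 30 = 30 minutes of moderate-to-vigorous activity. Nothing in the goal-setting step checks this.

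**4. Reset.** No arithmetic applies. Zeroing the counter when it is put on in the morning should cost little, since it has reset at midnight. Zeroing it later for the 10-minute walk could remove earlier steps from that day's bedtime reading. This is an inference: the protocol does not describe what a manual reset does to the display or to the stored daily value, so no size can be given.

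**The case against.** The strongest reply is that these are handout slips with little practical effect. Much of it stands.

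- **Cadence.** A reader might infer that participants are sent after an impossible pace. The text does not support that. They hold a 10-minute count and would naturally compare it with 1000, which gives the consistent rate. Other intensity cues exist: the brisk-walk and talk-but-not-sing guidance and the exertion scale in Appendix F, and the pace examples promised in Intervention Phase. The printed unit is still wrong against the next section.
- **Planner.** A reader might infer a 14-fold shortfall against what Hypothesis 2 scores. The 60 minutes a day is stated under Non-Hypothesis 3, the Hypothesis 2 paragraph gives no minutes figure, and 14 is the extreme of the range. The booklet also tells people to aim for the recommended daily minutes and allows a gradual start. The planner does not label its 30 as a starting or a daily figure, so the conflict remains. Both arms receive it, so it does not by itself bias the comparison between arms.
- **Tiers.** The jump at the boundary (4,999 + 6,000 = 10,999 against 5,000 + 3,000 = 8,000) may look like an error. Any banded rule produces a jump, and the handout says the amount depends on baseline. An added 30 minutes also matches the first recommendation listed in Appendix F. What stands is that the handout never says which recommendation its goal is equivalent to.
- **Reset.** A reader might infer that resetting is forbidden, or that it would cut the baseline day by half and move people across tiers. The protocol says only that it is unnecessary. The 10-minute walk is described after the baseline day has been recorded, and the rest depends on an assumed time of reset. Nor are the Non-Hypothesis 3 data shown to be affected: they come from the last week, whereas the set-up exercise belongs to the issue of the pedometer a week earlier.

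**Conclusion.** The concern holds as a fault in the participant materials, of minor to moderate severity. Three contradictions are in the current text:

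1. The printed cadence is ten times the rate implied by the handout's own step equivalent, although the likely way of using it gives the consistent figure.
2. The weekly planner is about 4 to 14 times below the 30- and 60-minute recommendations, assuming that most days means 4 to 7. In addition, the step goals are tied to an unnamed guideline, so a middle-tier participant could meet the written goal without reaching 60 minutes a day.
3. The reset instructions conflict. A loss of recorded steps is possible but inferred, and its size is unknown.

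What is at stake is the fidelity and clarity of the intervention. Hypotheses 1 and 2 are tested on accelerometer data; those tests, the alpha of 0.05 and the sample size of 60 do not change.

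**What to change.** Before the materials are distributed:

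- Reconcile Figuring out your steps, How many steps are enough?, Setting your goal, the recommendations list and planner in Appendix F, and the 60-minute figure in Statistical Analysis. Cadence, steps-to-minutes conversion and minutes target should agree with each other and with the recommendation that Hypothesis 2 scores. Setting your goal should name the recommendation it refers to. The sponsor decides which figures stand.
- Reconcile the reset wording in Beginning tomorrow, Figuring out your steps and the written pedometer instructions. One way to avoid a reset is to take the 10-minute count as end reading minus start reading.

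The cost is reprinting two handouts and notifying the IRB of the corrected materials. No analysis has to be changed.
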